# High-dose vitamin D substitution in patients with COVID-19: study protocol for a randomized, double-blind, placebo-controlled, multi-center study—VitCov Trial

**DOI:** 10.1186/s13063-022-06016-2

**Published:** 2022-02-04

**Keywords:** Coronavirus, SARS-CoV-2, COVID-19, Vitamin D, Vitamin D deficiency

## Abstract

**Background:**

The coronavirus disease 19 (COVID-19) pandemic has caused millions of deaths, and new treatments are urgently needed. Factors associated with a worse COVID-19 prognosis include old age (> 65 years), ethnicity, male sex, obesity, and people with comorbidities. Furthermore, vitamin D deficiency was reported as a predictor of poor prognosis in patients with acute respiratory failure due to COVID-19. According to a recent clinical case series, vitamin D deficiency is a modifiable risk factor, which has the prospect of reducing hospital stay, intensive care, and fatal outcomes. Vitamin D has potent immunomodulatory properties, and its supplementation might improve important outcomes in critically ill and vitamin D-deficient COVID-19 patients. Despite the evidence that supports an association between vitamin D deficiency and COVID-19 severity, there is uncertainty about the direct link. Therefore, the aim of the trial is to assess if high-dose vitamin D supplementation has a therapeutic effect in vitamin D-deficient patients with COVID-19.

**Methods:**

As the trial design, a randomized, placebo-controlled, double-blind, multi-center approach was chosen to compare a high single dose of vitamin D (140,000 IU) followed by treatment as usual (TAU) (VitD + TAU) with treatment as usual only (placebo + TAU) in patients with COVID-19 and vitamin D deficiency.

**Discussion:**

Vitamin D substitution in patients with COVID-19 and vitamin D deficiency should be investigated for efficacy and safety. The study aim is to test the hypothesis that patients with vitamin D deficiency suffering from COVID-19 treated under standardized conditions in hospital will recover faster when additionally treated with high-dose vitamin D supplementation. Latest studies suggest that vitamin D supplementation in patients with COVID-19 is highly recommended to positively influence the course of the disease. With this randomized controlled trial, a contribution to new treatment guidelines shall be made.

**Trial registration:**

ClinicalTrials.gov NCT04525820 and SNCTP 2020-01401

## Administrative information

Note: the numbers in curly brackets in this protocol refer to SPIRIT checklist item numbers. The order of the items has been modified to group similar items (see http://www.equator-network.org/reporting-guidelines/spirit-2013-statement-defining-standard-protocol-items-for-clinical-trials/).

## Introduction

### Background and rationale {6a}

A new coronavirus (CoV) infection epidemic began in Wuhan, Hubei, China, in late 2019, originally called 2019-nCoV [1] and renamed COVID-19 by the World Health Organization in 2020. Previous CoV epidemics included severe acute respiratory syndrome (SARS)-CoV in 2003 [2] and Middle East respiratory syndrome (MERS)-CoV in 2012 [3]. The mortality rates were > 10% for SARS and > 35% for MERS [4]. So far, this pandemic is responsible for millions of deaths. The direct cause of death is generally due to ensuing severe atypical pneumonia, followed by acute respiratory distress syndrome (ARDS) [4, 5].

Risk factors for a poor outcome of SARS-CoV-2 infection have so far been identified to include older age (> 65 years) and comorbidities such as chronic respiratory conditions, hypertension or diabetes, obesity, current smoking status, male sex, and Black or Asian ethnic origin [6–9].

Observational studies reported independent associations between low serum concentrations of 25-hydroxyvitamin D (the major circulating vitamin D metabolite) and susceptibility to acute respiratory tract infection [10–12]. 25-Hydroxyvitamin D supports induction of antimicrobial peptides in response to both viral and bacterial stimuli [6–8, 13], suggesting a potential mechanism by which vitamin D-inducible protection against respiratory pathogens might be mediated [14]. Previous studies observed that vitamin D deficiency is prevalent among patients with ARDS and other chronic respiratory diseases and likely contributes to its pathogenesis through alveolar-capillary damage [15, 16]. It was further reported that vitamin D is a predictor of poor prognosis in patients with acute respiratory failure due to COVID-19 [17–19]. Therefore, leading experts in the field have called for well-powered randomized controlled trials of vitamin D supplementation as an add-on treatment for COVID-19 to test for causality [20].

A randomized placebo-controlled trial of high-dose vitamin D in critically ill adult patients with vitamin D deficiency found a significant in-hospital mortality reduction among patients with severe vitamin D deficiency compared to placebo [21]. In a further study of vitamin D status in patients with ARDS, Park and colleagues retrospectively examined data from 108 patients with ARDS for whom a vitamin D status was available; they observed that over 95% of these patients had vitamin D deficiency [22]. When examined according to quartile of serum 25-hydroxyvitamin D, a consistent inverse relationship between serum 25-hydroxyvitamin D and length of hospital and ICU stay among survivors was observed [22].

A treatment with vitamin D showed a significant reduction of inflammatory markers, a shorter time to recovery for patients with cough, gustatory sensory loss in patients with COVID-19, and vitamin D deficiency, without the occurrence of side effects [23, 24]. The anticipated risk of side effects due to a single high dose of vitamin D in this study is minimal, compared to the potential impact on preventing more extended hospital stays and worse outcomes in COVID-19. A single high dose of vitamin D in addition to smaller daily doses is secure and can be added to the current treatment guidelines for COVID-19 [23]. Vitamin D supplementation is a safe and cost-effective intervention, with multiple health benefits for patients with COVID-19 and vitamin D deficiency [25].

### Objectives {7}

The primary objective of this study is to investigate if a single high dose of vitamin D, in addition to treatment as usual (TAU), reduces the length of the hospital stay in patients with COVID-19 and vitamin D deficiency. Furthermore, we have defined the following parameters as secondary outcomes: the necessity of ICU treatment, overall mortality, percentage of patients with 25-hydroxyvitamin D > 50 nmol/L (> 20 ng/mL) at day 7, changes in serum calcium, phosphorus, 25-hydroxyvitamin D, parathyroid hormone (PTH), and the development of sepsis. We hypothesized that time to recovery is shorter in the single high-dose vitamin D group relative to the standard treatment group.

## Methods: participants, interventions, and outcomes

### Trial design {8}

We decided to conduct the study as a randomized, placebo-controlled, double-blind trial. This study compares a single high dose of vitamin D in addition to treatment as usual (VitD + TAU) to placebo and treatment as usual only (placebo + TAU). Ethically, it is not justifiable not to treat a known vitamin D deficiency. Therefore, we decided to compare the intervention (single high dose of vitamin D) with treatment as usual (smaller daily dose of vitamin D). The study is designed as a superiority study that assumes, testing the hypothesis, that a single high dose of vitamin D in addition to TAU leads to faster recovery than treatment as usual only.

### Study setting {9}

It is planned to conduct the study in four cantonal hospitals in Switzerland—two in north-western Switzerland, one in the canton of Tessin, and one in eastern Switzerland. All hospitals are category A clinics; two of them are academic. If necessary, other hospitals are asked to participate.

### Eligibility criteria {10}

Participants are eligible to participate in the study after giving written, informed consent when hospitalized on a general medicine ward due to ongoing, PCR-confirmed SARS-CoV-2 infection, aged ≥18 years with laboratory-confirmed vitamin D deficiency defined as a serum 25-hydroxyvitamin D concentration ≤ 50 nmol/L (≤20 ng/mL). Patients will be included independently of the severity of the disease.

The presence of any of the following conditions will lead to the exclusion of the participant: known hypersensitivity to one of the vitamin D products used in this study or to one of the adjuvants in the drug’s composition, active malignancy, hypercalcemia, granulomatous diseases such as sarcoidosis, history of renal stones within the past year, pregnancy/breastfeeding, previous enrolment into the current project, or another interventional trial.

### Who will take informed consent? {26a}

After a patient is identified as a potential subject, all inclusion criteria are fulfilled, and none of the exclusion criteria is present, the patient will be asked by a study physician if they want to participate in this study. The patient then needs to give his written informed consent before the randomization. The study information and consent form are provided to the patient by the physician, and both documents are revised and approved by the responsible local ethics committee.

### Additional consent provisions for collection and use of participant data and biological specimens {26b}

It is not planned to collect data or biological material from participants, which is not described or mentioned in the study protocol or patient information. If there are changes in the protocol, participating subjects are provided with a new informed consent form to decide if they want to participate in further investigations.

### Interventions

#### Explanation for the choice of comparators {6b}

This study will be conducted as a randomized, placebo-controlled, double-blind trial comparing high-dose vitamin D in addition to TAU with placebo + TAU. The recommended supplementation of vitamin D in adults is 800 IU vitamin D3/day [26, 27].

As there is no ethical justification for not supplementing vitamin D in patients with laboratory-confirmed vitamin D deficiency, we decided against a “placebo only” design. Instead, we will compare single high-dose vitamin D + TAU versus placebo + TAU.

#### Intervention description {11a}

##### Intervention group

Participants will receive a single oral dose of 140,000 IU of vitamin D3 as an oily solution and then continue with the standard oral dose of 800 IU vitamin D3 per day until discharge. The medication will be administered by instructed personnel—preferably in the morning along with the patients’ other prescribed medication. We did not find information about significant differences resulting from the timing of administration.

##### Control group

Participants will receive a single dose of placebo orally and then continue with the standard dose of 800 IU vitamin D3 per day. The procedure of administration is the same as in the intervention group. The placebo solution is similar to the product used in the intervention group (VITAMIN D3 Wild Öl 500 IU/drop) in terms of consistency and look. Neither patients nor physicians can detect a difference between the two products.

#### Criteria for discontinuing or modifying allocated interventions {11b}

Treating doctors can change the dose of vitamin D or stop the treatment if clinically indicated. In such cases, it must be reported to the lead center immediately. The patient will be considered as a dropout. The treating physician can re-evaluate the treatment throughout the trial and independently decide about additional treatment options. The patient must be informed about all treatment options and must be treated according to the most recent local or national COVID-19 guidelines.

#### Strategies to improve adherence to interventions {11c}

Patient adherence is not assessed since the participants are all hospitalized, and qualified personnel will administer medication. The nurses and doctors will ensure that the patient receives the study medication correctly. If there is any complication with the administration (e.g., vomiting after taking the study medication), it must be reported directly to the lead center. The local study team will collect the used medication bottles and, if needed, can be used for additional evaluation of adherence after the patient is discharged.

### Relevant concomitant care permitted or prohibited during the trial {11d}

All treatments or medication considered necessary by treating doctors are permitted, and their use will be recorded in the case report form. There is no restriction in using other treatments or interventions during this trial.

### Provisions for post-trial care {30}

Patients are carefully followed up until discharge from hospital care. Any after-care necessary due to COVID-19 is organized by the treating physicians and is not connected to this trial. This trial has a mandatory, trial-specific insurance during the whole study period.

### Outcomes {12}

As the primary outcome, we fixed the length of the hospital stay. Therefore, the measurement will be the overall duration of the hospitalization from enrolment until discharge from hospital care. As defined, to measure the secondary objectives, we will assess if there are any differences between the TAU + VitD and the TAU + placebo group in terms of the variables described in the table below.

**Table Tabb:** 

ICU stay	Yes/no
	If yes, length of the ICU stays (admission to discharge)
	Requirement for mechanical ventilation
Overall mortality	
Vitamin D serum concentration	% of patients with 25-(OH)D > 50 nmol/L at day 7
	25-(OH)D
Laboratory parameters	Calcium
	Phosphorus
	Parathyroid hormone (PTH)
Sepsis	% of patients who develop a sepsis
Complications	Complications during the hospitalization due to COVID-19
Vital signs	Blood pressure (BP)
	Heart rate (HR)
	Respiratory rate (RR)
	Blood oxygen saturation
	Need of oxygen and how much
Quality of life (SF-12 Questionnaire)	At baseline, 28 days, and 3 months after inclusion

### Participant timeline {13}

### Sample size {14}

To calculate the sample size, we looked at an interventional study of vitamin D, which examined the length of hospital stay as an outcome and what is known about the median length of hospital stay in patients hospitalized with COVID-19. A randomized, double-blind, placebo-controlled trial examined the effects of adjunctive vitamin D in adults hospitalized with community-acquired pneumonia (CAP) on time to recovery [28]. The primary outcome was the complete resolution of chest radiograph infiltrates at 6 weeks post-study treatment. Secondary outcomes included length of hospital stay, intensive care admission, and return to regular activity. At the same time, adjunctive vitamin D did not affect the primary outcome (*OR* 0.78, 95% *CI* 0.31 to 1.86, *p* = 0.548). There was evidence it increased the complete resolution of pneumonia in participants with baseline vitamin D levels < 25 nmol/L (*OR* 17.0, 95% *CI* 1.40–549.45, *p* = 0.043). Although not significant, the results indicated that patients in the intervention group had shorter length of hospital stay (mean = 3.8, *SD* = ± 3.1, *n* = 60) when compared with patients in the placebo group (mean = 4.8, *SD* = ± 6.5, *n* = 57), which indicates a small effect size (Cohen’s *d*) of 0.1980. The study indicated a 20% reduction in length of hospital stay.

Considering the above results in the light of COVID-19, more extended hospital stays in COVID-19 patients are expected. In smaller observational studies describing the clinical course of hospitalized COVID-19 patients in China, a median hospital stay of 12 days (*IQR* 9–15) (*n* = 137) [1] or of 10 days (*IQR*, 7.0–14.0) among those discharged alive (*n* = 47) [29] were observed. Guan et al. presented the clinical characteristics of 1099 patients with laboratory-confirmed COVID-19, and the median length of hospital stay was reported to be 12 days (*IQR* = 10–14) [30], which we will take as a basis for our sample size calculation.

Sample size calculation was performed using the function “power.t.test” from the R package “stats” with the following parameters [31]: alpha = 0.05, power = 0.80, sigma = 2.96, delta (difference in the primary outcome between intervention and control group) = 2, and alternative hypothesis = two-sided, which resulted in a minimum of 35 patients per group, therefore a total of 70 patients. With a conservatively estimated 10% dropout rate, including the loss to follow-up, and a block size randomization of four, we decided to include 80 patients.

### Recruitment {15}

After a patient is identified as a potential participant, all inclusion criteria are fulfilled, and none of the exclusion criteria is present, the patient will be asked by their treating physician if they want to participate in this study.

Only patients on general wards will be asked. Patients who are already being treated in the intensive care unit or taking part in another interventional trial will not be considered as potential participants. Neither patients nor doctors will receive financial reimbursement. The study budget will cover expenses for the study medication and diagnostics performed only during this study. The recruitment will take place in the described way in all four centers (cantonal hospital of Baselland in Liestal and Bruderholz, the cantonal hospital of Aarau, the cantonal hospital of St. Gallen, and the regional hospital Lugano). A collaboration with other hospitals in Switzerland will be considered if recruitment is slow.

### Assignment of interventions: allocation

#### Sequence generation {16a}

Participants will be randomly assigned to either the intervention or the control group in a 1:1 ratio. A statistician not involved in the data analysis generates a randomization list with study group allocation using R [31]. Randomization is carried out stratified by center using block randomization with a block size of four to account for differences in standard of care. The randomization master list will be handed over to the university hospital pharmacy in Basel, where the study drug will be labeled and packaged accordingly. In case of an adverse event (AE) or serious adverse event (SAE) that requires an emergency code break, the hospital pharmacy can decode the randomization immediately.

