### Statistical methods

#### Statistical methods for primary and secondary outcomes {20a}

A statistical analysis plan documented detailed methodology for summaries and statistical analyses of the data collected in this trial. The statistical analysis plan is finalized analysis [31]. We will summarize our results using descriptive statistics.

The primary analysis comparing the mean length of hospital stay between the two groups will be performed on the dataset of all randomized patients for whom the outcome measure is available. A two-sided independent Student’s *t*-test will be used following log-normal transformation as Feng et al. [32] suggested. The time to discharge will be assessed up to 3 months, with failure to reach discharge or die before that day considered as right censored at 3 months. Patients who are admitted to ICU or change wards within the hospital can continue the study and their data can be analyzed as planned, since the intervention can be continued, and daily visit data are available within the electronic patient documentation system. For patients who are transferred to another hospital, the primary endpoint will be taken from the respective discharge letter, which is by standard sent from the following hospital to the referring hospital. If this data is not available, the patient will be considered as right censored at the date of transfer.

In the secondary outcome analyses, mean levels of calcium, phosphorus, 25-hydroxyvitamin D, 1,25-dihydroxy vitamin D, and PTH will be compared using two-sided independent Student’s *t*-tests. To compare the proportion of patients who died, were admitted to ICU, developed sepsis, and as the proportion of patients with 25-hydroxyvitamin D ≥ 30 ng/mL at discharge between the two groups, either the χ ^2^ test or the Fisher exact probability test will be used. The Fisher exact probability test is an excellent non-parametric technique for comparing proportions when the two independent samples are small.

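### Randomisation is stratified by centre, but the fixed primary t-test leaves centre out: the test is mildly conservative and gives up about 1 to 5 power points that could be had at almost no cost

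*Protocol article*

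**What the plan says.** Under Sequence generation {16a} the article says: "Randomization is carried out stratified by center using block randomization with a block size of four to account for differences in standard of care". The plan therefore expects hospitals to differ in a way that matters. Study setting {9} and Recruitment {15} name four centres, one of them with two sites.

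Under Statistical methods {20a} it says: "The primary analysis comparing the mean length of hospital stay between the two groups will be performed on the dataset of all randomized patients" with an available outcome. It names the test as a two-sided independent Student's t-test after log transformation. No centre term and no baseline covariate is mentioned. Mixed-effect models appear only for safety parameters, and sex and baseline vitamin D only as optional subgroup factors ({20b}). The sample size ({14}) rests on the same unadjusted t-test.

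On the spread of prognosis, Eligibility {10} says: "Patients will be included independently of the severity of the disease". Recruitment {15} narrows this to general-ward patients and excludes those already in intensive care.

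**The concern.** Stratified blocks force each centre to contribute almost equal numbers to both arms, so differences between centres largely cancel out of the treatment comparison. The pooled t-test still counts those differences in its error variance. Its standard error then describes a trial randomised without strata, not this one. Length of stay is an outcome on which local care and discharge practice could plausibly act, and the article gives differing care as the reason for stratifying.

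At stake are a confidence interval wider than it should be, a true significance level below the nominal 5%, and some lost power in an 80-patient trial. A second, separate loss is that prognostic baseline values are not used to reduce residual variance.

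**Working it through.** **1. Reproduce the planned sample size.** The inputs in Sample size {14} are "alpha = 0.05, power = 0.80, sigma = 2.96", "delta (difference in the primary outcome between intervention and control group) = 2" and "alternative hypothesis = two-sided". The SD comes from the IQR of 10–14 days in the study adopted as the basis: 4/1.35 = 2.96. The standardised effect is 2/2.96 = 0.676. The normal approximation gives 35 per group, which matches "resulted in a minimum of 35 patients per group, therefore a total of 70 patients". The exact noncentral-t solution is 35.37, so 36 when rounded up; 35 per group gives 79.6% power. For dropout, 72/0.90 = 80, which fits the final figure of 80.

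**2. Standard error with 72 evaluable patients (36 per arm).** Let ρ be the share of outcome variance explained by centre. The article gives no value, so 0–20% is assumed.

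- The SE that the t-test reports is about 2.96 × √(2/36) = 0.698, whatever ρ is.
- The true SE under centre-stratified allocation is about 0.698 × √(1 − ρ).
- ρ = 5%: 0.698 × 0.975 = 0.680.
- ρ = 10%: 0.698 × 0.949 = 0.662.
- ρ = 20%: 0.698 × 0.894 = 0.624.

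The critical value 1.96 therefore acts like 1.96/√(1 − ρ), which is 2.011, 2.066 and 2.191. The corresponding two-sided normal tail areas are 4.4%, 3.9% and 2.8%.

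**3. Simulation.** Four centres (20, 16, 20 and 16 patients), permuted blocks of four, SD 2.96, difference 2 days, 8,000 runs per scenario. Monte Carlo uncertainty on power is about 0.8 points.

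| Assumed centre share | Type I error: t-test / with centre | Power: t-test / with centre |
|---|---|---|
| 0% | 4.6% / 4.6% | 80.7% / 80.7% |
| 5% | 4.8% / 5.5% | 81.3% / 82.7% |
| 10% | 4.0% / 5.1% | 81.7% / 84.4% |
| 20% | 2.8% / 5.0% | 83.3% / 88.5% |

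The t-test's mean reported SE was 0.696 at both 10% and 20%, against true values of 0.663 and 0.627. This agrees with step 2. The gain from adding centre is 1.4, 2.7 and 5.2 points at shares of 5%, 10% and 20%. With no centre effect, the degrees of freedom lost cost about 0.1 point.

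**4. Log scale, where the test is actually run.** Taking the same adopted study and a fall from 12 to 10 days, the effect is ln(12/10) / (ln(14/10)/1.349) = 0.182/0.249 = 0.73 SD. With all 80 patients in four centres of 20 (20,000 runs), power without and with centre is 89.7% and 89.7% at a 0% share, 90.8% and 91.6% at 5%, 91.1% and 92.8% at 10%, and 92.1% and 95.2% at 20%. The gain is about 1 to 3 points.

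**5. Adding one baseline covariate.** In the day-scale simulation, a covariate explaining an assumed 20% of variance raises power beyond centre adjustment from 83.3% to 90.4% (centre share 5%), from 84.3% to 91.5% (10%) and from 88.3% to 95.1% (20%). That is about 7 points here, so roughly 5 to 8 at the planned effect, and less where power already exceeds 90%. This is an efficiency gain only. Randomisation did not balance these factors by design, so the unadjusted SE is valid with respect to them.

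**The case against.** The strongest reply is that nothing here is invalid. An unadjusted comparison in a randomised trial is unbiased, its error is on the cautious side, and power on the plan's own inputs stays near 80% or above. The gain from centre is small and vanishes if centres do not differ. All of that stands, and it limits the weight of the point.

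Three stronger readings are tempting but not supported.

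- A reader might infer that the trial has only about 56% power, rising to 72–76% with adjustment. Those figures need an effect of ln(12/10) / (ln(15/9)/1.349) = 0.48 SD. The IQR of 9–15 behind it belongs to another, smaller study that Sample size {14} cites but does not adopt. They describe a smaller-effect scenario, and leaving out centre does not produce the 56%.
- A reader might infer that ignoring any prognostic factor makes the standard error wrong. That holds for centre alone, because only centre was used in the allocation.
- A reader might infer that entry severity is unlimited and that baseline oxygen need is available. Intensive-care patients are excluded at entry. Oxygen need is listed as an outcome, and the text shown states no baseline time point for it.

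It may also be said that the separate analysis plan, described as finalised but not shown, could include centre. The article nonetheless names the primary test explicitly, so this is a stated choice and not an omitted detail.

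**Conclusion.** The mismatch is real and modest. The article stratifies by centre for a stated reason and then fixes a primary test that discards centre. If centre matters, the reported standard error is too large, and the true type I error is about 4–5% at an assumed centre share of 5–10% and about 3% at 20%. Including centre gains about 1 to 5 power points on the day scale and about 1 to 3 on the log scale. Every figure depends on assumed variance shares and on close balance within centres. The conclusion does not extend to bias, to inflated type I error or to a shortfall against the planned power. The case for other covariates is a recommendation on efficiency, not a correction of an error.

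**What to change.** Make the primary analysis a linear model on log length of stay with treatment and centre, using the centre strata of the randomisation list. If stay is instead analysed as time to discharge, use a centre-stratified model. Add age and screening 25-(OH)D, and baseline oxygen need only if it is recorded at inclusion. Fix the covariates and their form before unblinding, and report the unadjusted t-test as supportive.

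For centre, age and 25-(OH)D no new data are needed, since all three are known at enrolment. The cost is an amendment to an analysis plan described as finalised, reported to the ethics committee as {20c} requires. Trial status puts the last inclusion in mid-September 2021, so this works only if the data are still blinded. Otherwise, show the centre-adjusted result as a labelled sensitivity analysis.
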